#### Primary outcome

The primary outcome is the change in physical performance measured with the Modified Physical Performance Test (M-PPT), between baseline and 6 months [28, 29]. The M-PPT will be performed as an assessment of multiple dimensions of physical function (basic and complex activities of daily living) with different levels of difficulty. The test is well-known in elderly research [30, 31]. The test consists of 9 items [28, 32]; 1. Book lift; 2. Put on and take off a coat; 3. Pick up a coin; 4. Chair rise; 5. Turn 360°; 6. 15.2 m walk; 7. One flight of stairs; 8. Four flights of stairs; 9. Progressive Romberg test. The maximum score is 36; 4 points per item. The test takes approximately 10 to 15 min.

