### Planned statistical analyses

The sample size calculation for the primary outcome parameter is based on the modified Physical Performance Test (M-PPT) of Villareal et al. [29] using the following estimates: Effect size: 1.7 points mean difference in physical performance (M-PPT), a standard deviation (SD) of difference of 1.75, an average cluster size of 10, with an ICC of 2.5. Using the above-mentioned estimates, a significance level (α) of 0.05 and a power of 80%, a sample size of 56 per group is estimated to be sufficient to detect a statistically significant difference in physical performance after 6 months between groups. Assuming 40% drop-out, a total number of 78 subjects is needed per group. Therefore we aim to include 80 subjects per group and in total 240 subjects.

Summary statistics (mean, median, standard deviation, and frequency distribution) will be generated for baseline characteristics. To compare the baseline characteristics between the 3 groups, one-way ANOVA or Kruskal-Wallis test will be used for continuous variables, and Chi-square or Fisher’s exact tests, for categorical variables. Changes in M-PPT, secondary and explorative outcomes will be visualised over the entire time course using mean and standard error of the mean (SEM) per treatment group.

Data will be analysed in accordance with the research questions outlined in the introduction, applying appropriate Linear Mixed Models. Differences within and between treatment groups in the outcome parameter will be analysed. Time, treatment and their interaction will be defined as fixed factors. Subject and group will be included as random factor. If imbalances occur between groups despite randomisation, the baseline values will be treated as covariates.

Detailed analyses will be stated in the Statistical Analysis Plan, which will be finalised before unblinding of the study. All statistical analyses will be performed using SPSS Statistics v22 (IBM, USA). An α of 0.05 will be used to determine statistical significance.

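### Read as intercepts, the random effects named for subject and group do not protect the 6-month M-PPT change contrast against clustering of change, which the sample size itself assumes

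*Protocol article*

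**What the plan says.** Under Study design and setting and under Procedures, existing weekly exercise groups are the units that are randomised to the three arms. Under Primary outcome the endpoint is a change score: "The primary outcome is the change in physical performance measured with the Modified Physical Performance Test (M-PPT), between baseline and 6 months".

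Under Planned statistical analyses the article says four things that bear on this point:

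- The sample size rests on "a standard deviation (SD) of difference of 1.75, an average cluster size of 10", an ICC printed as 2.5, a difference of 1.7 points, α of 0.05 and 80% power. It arrives at 56 per group before dropout.
- The model for the outcomes is: "Time, treatment and their interaction will be defined as fixed factors. Subject and group will be included as random factor".
- Baseline adjustment is conditional: "If imbalances occur between groups despite randomisation, the baseline values will be treated as covariates".
- Further detail is deferred: "Detailed analyses will be stated in the Statistical Analysis Plan, which will be finalised before unblinding of the study".

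No cluster-by-time term or random slope is named. The words for intercept or for exclusivity do not appear either.

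**The concern.** In a repeated-measures model with baseline among the outcomes, the treatment effect on 6-month change is the time-by-treatment coefficient. A random cluster intercept describes clusters that are persistently fitter or less fit. It does not describe clusters that improve, or fail to improve, together. In a cluster trial of change, it is the second kind of similarity that inflates the variance of the treatment contrast.

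The plan expects that second kind, because it pairs a cluster size and an ICC with the SD of a difference. If the analysis then carries only intercepts, the design effect that produced the sample size is absent from the test it was meant to support. The standard error, confidence interval and p-value of the primary comparison would then be too small whenever changes are correlated within exercise groups.

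The label adds to the difficulty. Elsewhere in the same section *group* mostly means the trial arm, and the exercise groups appear as clusters. A programmer could enter the arm as the random factor, in which case the clusters would not be in the model at all.

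**Working it through.** **1. Reproduce the plan's figure.** Inputs from Planned statistical analyses: difference 1.7, SD of difference 1.75, α 0.05 (two-sided assumed), power 80%, cluster size m = 10.

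Individual randomisation: n = 2 × (1.75 × (1.960 + 0.842) / 1.7)² = 16.6, so 17 per arm. Design effect: 1 + (m − 1) × ICC.

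| ICC | Design effect | n per arm |
|---|---|---|
| 2.5 (as printed) | 23.5 | 17 × 23.5 = 399.5, so 400 |
| 0.25 | 3.25 | 17 × 3.25 = 55.25, so 56 |
| 0.025 | 1.225 | 17 × 1.225 = 20.8, so 21 |

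Only 0.25 gives the stated 56. It is an inference from the arithmetic and is not printed in the article. The design effect is applied to the SD of change.

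**2. What the named random effects do to the contrast.** For subject i in cluster j at visit t, with intercepts only:

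Y(ijt) = fixed part + c(j) + s(ij) + e(ijt)

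Change to 6 months = fixed part + e(ij6) − e(ij0)

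Both c(j) and s(ij) cancel. With complete data the standard error of the contrast between two arms is 1.75 × √(2/n), the formula for unclustered individuals. At 56 per arm it is 1.75 × √(2/56) = 0.3307. The exact generalised least squares standard error is 0.3307 whether the cluster-intercept variance is set to 0, 1 or 5. With 8 clusters of 10 per arm and about 40% dropout it still hardly moves (0.3021 to 0.3022).

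**3. Add a cluster-by-visit effect g(jt).** The change now contains g(j6) − g(j0), which cluster members share. Keep the SD of change at 1.75 and let ρ be the ICC of change. Then SE = 1.75 × √(2/n × (1 + (m − 1)ρ)). With ρ = 0.25 and 8 clusters per arm (80/10):

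| Analysed per cluster | n per arm | SE, intercepts only | SE with cluster-by-visit effect | Ratio |
|---|---|---|---|---|
| 10 | 80 | 0.277 | 0.499 | 1.80 = √3.25 |
| 7 | 56 | 0.331 | 0.523 | 1.58 = √2.5 |

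**4. Consequence for a nominal 5% test.** If the design effect D is left out, the true error is 2 × (1 − Φ(1.96/√D)).

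| Assumed ICC of change | m = 10 | m = 7 |
|---|---|---|
| 0.25 | 27.7% | 21.5% |
| 0.10 | 15.5% | 12.1% |
| 0.05 | 10.4% | 8.6% |
| 0.025 | 7.7% | 6.8% |

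Simulation at ICC 0.25 gave 28.0% (m = 10) and 21.8% (m = 7). Cluster-level tests of change held about 5%.

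**5. Does the baseline covariate help?** That depends on whether baseline also leaves the outcomes.

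- If baseline M-PPT is added as a covariate while the baseline visit remains an outcome, the covariate is constant within a person and cancels as well. In 60 simulated null trials (ICC 0.25, 8 clusters of 10 per arm, three visits) the mean SE was 0.272 without and 0.273 with the covariate, and 17 and 16 trials respectively rejected.
- If the 6-month value is the outcome and baseline only a covariate, the cluster intercept does not cancel. Simulated error was about 3% in 200 runs, too few to tell from 5%.

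**The case against.** The strongest reply is that the article does not say what the criticism needs. The sentence "Subject and group will be included as random factor" specifies neither intercepts nor the absence of further terms. The same paragraph calls for suitable mixed models, and detail is left to an analysis plan that is not shown. Cluster-by-visit terms and degrees of freedom are things such a plan often supplies. This stands in part. It makes the fault conditional, but it does not remove it: the article chose to state a random structure, and an analysis plan that follows it in the ordinary way inherits the problem.

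A second reply is that the plan provides for baseline covariates. It does so only if imbalance is seen, and it does not say that the baseline visit then leaves the outcomes, which is what makes the difference.

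A third reply is that the random *group* is naturally the exercise group, because treatment has just been listed as fixed. That is the likelier reading, and the calculation above adopts it. The cancellation occurs all the same.

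A fourth reply is that the added training is done at home and coached individually, so changes may be only weakly correlated. That is possible, and it is why a range is shown. It sits badly, though, with a sample size that assumes a large correlation of changes.

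Two stronger readings should be resisted. A reader might infer that the trial will be analysed as if individuals had been randomised. The article does not say so: it names a random group factor, and one permissible version of its model lets that factor act. A reader might also infer that the planned plots of means with SEM are part of the fault. They are descriptive and change no test.

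**Conclusion.** The point holds conditionally. With the named random effects taken as intercepts and baseline kept among the outcomes, the primary time-by-treatment contrast has no protection against clustering of change, and the design effect behind 56 per group is missing from the analysis. For complete data this is exact algebra.

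The size depends on the ICC of change, for which the article gives no usable value. The figures of about 1.8 for the standard error and about 28% for the error rate rest on ICC 0.25, 10 analysed per cluster and a two-sided test. They should not be read as the expected error of this trial. At an ICC of 0.025 the error would be 7.7% with 10 per cluster. It exceeds 5% at any positive ICC of change, and because this is the primary test it should be settled before the analysis plan is finalised.

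**What to change.** Define the random factor *group* as the weekly exercise group (cluster), then choose one of two models and state it in full:

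- keep baseline among the outcomes and include random effects for cluster, cluster-by-visit and subject within cluster; or
- model the 6- and 12-month M-PPT values with baseline M-PPT as covariate, whatever imbalance is observed, with random cluster and cluster-by-visit effects and subject within cluster.

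In either case use small-sample (Satterthwaite) degrees of freedom, because at about 10 per cluster there are only some 24 clusters (240/10). Correct the printed ICC at the same time, so that the analysis and the sample size can be seen to rest on the same assumption.

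The cost is one further random term in the SPSS mixed model and a sentence of text. Confidence intervals become wider. On the plan's own figures that width is already paid for: 56/3.25 = 17.2 effective participants per arm gives about 81% power for 1.7 points by the normal approximation.

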## Discussion

As the society ages, there is a demand for practical and innovative interventions to reduce the decline in physical performance and maintenance of muscle mass, strength and physical performance in the ageing population. Because earlier research on weekly group exercise remained ineffective on physical performance, we have developed an innovative modular approach based on a new home-based personalised training program with functional ADL based exercises. Furthermore, the dietary counselling and the overall coaching is personalised. Especially, the persuasive technology underlying our digital support improves personalisation. Besides personalisation, our digital support improves insight in the compliance and provides the opportunity to monitor progression in the training of the participant. We are interested in both the effect at 6 months coached intervention as well as 12 months follow-up retention of intervention effect.

A factor that may be considered a threat to this intervention is the inclusion of participants of regular weekly exercise groups. This approach is an easy to implement choice, since the presently existing structure and participation in the Netherlands could be updated with a more effective form of weekly exercise with added digitally supported home based exercise. However, this also requires the cooperation and time of trainers as well as consent of some involved organisations. Also, the regular exercise groups are usually indicated for older adults with some decline in physical performance however, because of the important social component of these groups also a fitter group of older adults might participate. Since, we aimed for a broad national implementation we did not exclude the more fit and able, while we intend a per protocol analysis for those older adults with declined physical functioning.

Since the digital application is developed and a small pilot study has been conducted before start of the trial, potential issues with the interventions need to be taken into account. Therefore, suboptimal performance of the digital application might contribute to a smaller effect of the intervention on physical performance.

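### As written, the mixed model handles the three M-PPT measurements only through a random subject factor; in the ordinary reading this gives every between-visit change the same variance, which the design gives no reason to expect

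*Protocol article*

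**What the plan says.** Under Planned statistical analyses, the protocol article gives the fixed part of the model as "Time, treatment and their interaction will be defined as fixed factors" and the random part as "Subject and group will be included as random factor". It names no residual covariance structure, random slope or visit-specific variance. The models are introduced as "applying appropriate Linear Mixed Models", and further detail is deferred: "Detailed analyses will be stated in the Statistical Analysis Plan, which will be finalised before unblinding of the study". Baseline may become a covariate: "If imbalances occur between groups despite randomisation, the baseline values will be treated as covariates".

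Two contrasts depend on this model. Under Primary outcome: "The primary outcome is the change in physical performance measured with the Modified Physical Performance Test (M-PPT), between baseline and 6 months". In the Discussion: "We are interested in both the effect at 6 months coached intervention as well as 12 months follow-up retention of intervention effect". The sample size rests on one change SD, "a standard deviation (SD) of difference of 1.75", for the comparison at 6 months. No SD is given for the 0-12 or 6-12 month change. Table 3 confirms that M-PPT is taken at all three visits.

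**The concern.** The random subject factor is the only device the article names for the dependence among one person's three measurements. With a random intercept and independent residuals of one variance, all visits have the same variance and all pairs of visits the same correlation. Every within-person change then has the same model variance, whichever two visits it spans.

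The design does not suggest that the changes are equally variable. Months 0-6 are the coached intervention, with individually tailored and diminishing contact. Months 6-12 are follow-up. The pairs of visits are 6 or 12 months apart. If the true change variances differ, the standard error of the 6-month primary contrast borrows from the 0-12 and 6-12 month changes and no longer reflects the SD behind the sample size, and the 12-month standard error is distorted in turn. One test may be too strict and the other too lenient, or both may be too lenient. This concerns repeated measures within a person and arises even without clustering by exercise group.

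**Working it through.** **The plan's own figure.** A difference of 1.7, SD 1.75, two-sided alpha 0.05 (sidedness is assumed) and 80% power give 2 × (1.75 × 2.80 / 1.7)² = 16.6, so 17 per group. The design effect for clusters of 10 is 1 + 9 × ICC. The printed ICC of 2.5 gives 17 × 23.5 = 399.5, so 400, not the stated 56. Read as 0.25 it gives 17 × 3.25 = 55.25, so 56. The ICC is a separate matter. What counts here is that 56 rests on 1.75 as the SD of the 6-month change.

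**What a random intercept does to the change variances.** Let V06, V012 and V612 be the true variances of the three changes. With complete data:
- A person's within-person sum of squares over three visits is one third of the sum of the three squared differences, so its expectation is (V06 + V012 + V612)/3.
- It carries 2 degrees of freedom, so the residual variance has expectation (V06 + V012 + V612)/6.
- The model variance of any change is twice that: M = (V06 + V012 + V612)/3.
- The ratio of model SE to true SE is r = √(M/V), and the actual two-sided false-positive rate is 2 × (1 − Φ(1.96 r)).

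**Inputs.** The 0-6 month SD of 1.75 is the plan's. The other SDs are assumptions. Retention is taken as the 0-12 month change. Data are complete and there is no cluster effect.

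*Case A: 0-12 month SD 2.2, 6-12 month SD 1.75.* M = (3.0625 + 4.84 + 3.0625)/3 = 3.655, pooled SD 1.912.
- 6 months: r = 1.912/1.75 = 1.092, false-positive rate 3.2%.
- 12 months: r = 1.912/2.2 = 0.869, false-positive rate 8.9%.
- Power at 6 months, if 80% with the correct SE: Φ(2.80 − 1.96 × 1.092) = Φ(0.66), about 75%.

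*Case B: 0-12 month SD 1.75, 6-12 month SD 1.2.* M = (3.0625 + 3.0625 + 1.44)/3 = 2.522, pooled SD 1.588.
- 6 and 12 months: r = 1.588/1.75 = 0.907, false-positive rate 7.5% for both.
- 6-12 month change: r = 1.588/1.2 = 1.323, an SE 32% too large.

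*Case C: all three SDs equal.* r = 1 throughout and the rate is 5%.

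**Range.**

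| Assumption | 6-month SE ratio | 6-month rate | 12-month SE ratio | 12-month rate |
|---|---|---|---|---|
| First-order autoregressive, correlation 0.5 | 1.08 | 3.4% | 0.88 | 8.4% |
| Same, 0.7 | 1.11 | 3.0% | 0.85 | 9.5% |
| Same, 0.9 | 1.14 | 2.5% | 0.83 | 10.5% |
| Grid: SD(0-12)/SD(0-6) 0.8 to 1.4, SD(6-12)/SD(0-6) 0.8 to 1.2 | 0.87 to 1.21 | 8.8% to 1.8% | 0.78 to 1.27 | 12.5% to 1.3% |

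A simulation of 4,000 complete-data trials with 80 per arm and autoregressive correlation 0.7 gave 3.1% at 6 months and 9.4% at 12 months, in line with the formula.

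**The case against.** The strongest objection is that the article does not commit to this model. It never says random intercept only, independent residuals or compound symmetry. It speaks of appropriate models and sends detail to a statistical analysis plan that is not shown, where the within-person covariance is commonly settled. SPSS MIXED also accepts a random effect and a residual structure together. A reader might infer that the protocol forces compound symmetry, and the text does not support that. A random subject factor with visit-specific residual variances, for instance, could be fitted and would relax the constraint.

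The objection does not remove the point. The article does name the model terms, and the subject factor is the only one that deals with repeated measures. An analysis plan that merely follows the sentence inherits the constraint. Nor can an unstructured residual simply be added: with three visits there are six variances and covariances, and a random intercept plus an unstructured residual has seven parameters, so it is not identifiable. The subject factor has to be replaced.

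Four further limits stand:
- The only change SD in the article is 1.75. The others are assumed, and equal variances give no error.
- For the 6-month contrast alone, V06 need only equal the average of the three. Variances of 1.0, 1.3 and 0.7 give a correct 6-month SE.
- The calculations leave out clustering and drop-out, so the rates illustrate the mechanism and do not predict this trial's error rates.
- If baseline becomes a covariate and leaves the outcome vector, two visits remain and the averaging of three changes no longer applies. A random intercept then still imposes equal residual variances at 6 and 12 months.

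**Conclusion.** The point holds conditionally. In the ordinary reading of the stated random factor, the three changes share one variance, and the 6- and 12-month standard errors are both correct only if the three change variances are equal. The design gives no reason to rely on that.

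A reader might go further and infer that the trial's standard errors and p-values are wrong. The documents do not show this: they contain no later change SDs or correlations, and the analysis plan may choose another structure. Nor does the primary test necessarily suffer inflation. In Case A and under the autoregressive assumptions it is conservative, and the inflation falls on 12-month retention. It is inflated in Case B, where the 6-12 month change is the less variable one.

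Under the declared assumptions the distortion is about 9% in the 6-month SE in either direction, and 9% to 13% too small in the 12-month SE. The nominal 5% becomes about 3% or 7.5% at 6 months and about 7.5% to 9% at 12 months. This is a cheap improvement, not a demonstrated error.

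**What to change.** Before unblinding, state in the statistical analysis plan that the random subject factor is replaced by an unstructured 3 × 3 covariance over the visits within participant. In SPSS MIXED this is a REPEATED statement on visit, with participant as subject and COVTYPE(UN). Keep the random exercise-group effects for the clustering. If baseline is moved to the covariates, use the same structure over the two remaining visits.

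Each change then has its own variance, so the 6-month contrast again rests on the variance of the 0-6 month change, the quantity behind the sample size. The cost is a line of wording and four more covariance parameters (six within-person parameters in place of two), which is modest with 240 planned participants and three fixed visits.

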## Discussion

As the society ages, there is a demand for practical and innovative interventions to reduce the decline in physical performance and maintenance of muscle mass, strength and physical performance in the ageing population. Because earlier research on weekly group exercise remained ineffective on physical performance, we have developed an innovative modular approach based on a new home-based personalised training program with functional ADL based exercises. Furthermore, the dietary counselling and the overall coaching is personalised. Especially, the persuasive technology underlying our digital support improves personalisation. Besides personalisation, our digital support improves insight in the compliance and provides the opportunity to monitor progression in the training of the participant. We are interested in both the effect at 6 months coached intervention as well as 12 months follow-up retention of intervention effect.

A factor that may be considered a threat to this intervention is the inclusion of participants of regular weekly exercise groups. This approach is an easy to implement choice, since the presently existing structure and participation in the Netherlands could be updated with a more effective form of weekly exercise with added digitally supported home based exercise. However, this also requires the cooperation and time of trainers as well as consent of some involved organisations. Also, the regular exercise groups are usually indicated for older adults with some decline in physical performance however, because of the important social component of these groups also a fitter group of older adults might participate. Since, we aimed for a broad national implementation we did not exclude the more fit and able, while we intend a per protocol analysis for those older adults with declined physical functioning.

Since the digital application is developed and a small pilot study has been conducted before start of the trial, potential issues with the interventions need to be taken into account. Therefore, suboptimal performance of the digital application might contribute to a smaller effect of the intervention on physical performance.

The findings of this study are relevant for future developments in health and community care and professional education. Also the designed technology provides new opportunities for application designers. The VITAMIN study will provide novel insights in the impact of home-based exercise, protein intake and use of technology in the population of community dwelling older adults.

